### Recruitment

It was estimated that 22 months would be needed to recruit the total sample of 258 at a recruitment rate of 12 children per month. Such rates are similar to other studies of children with neurodisability [38]. Data from the participating sites suggest they receive in excess of 100 referrals a year (and as many as 300), at least a third of whom could be eligible for the study. Therefore, recruitment of the required number of participants within this age range was deemed feasible. A multisource referral strategy is being followed, facilitated by the clinical research networks, national, clinical and third sector contacts, as well as social media. Participants receive £15 vouchers at each assessment time point for time donated to the study. In addition, child care and travel for participants may also be reimbursed where appropriate.

### Methods – assignment of interventions

#### Allocation

Participants are randomised using a 3:2 allocation ratio to either SSTP or TAU using randomly permuted blocks of varying block sizes and stratification by site and level of ID (moderate and severe). Randomisation and data management is provided by Sealed Envelope [39], a commercial clinical randomisation and data management web service.

#### Allocation concealment and implementation

Research assistants enter baseline assessment results on a web-based case report form (CRF). Each case is assigned a study number and parents and therapists are given information about allocation status. Arrangements are then made to commence the group sessions. Researchers are in separate departments than staff involved in delivery of level 4 SSTP. The therapists do not treat any families allocated to TAU.

#### Blinding

Although it is not possible to blind trial participants or therapists delivering the intervention, parents are reminded not to disclose any details about their treatment to the research team during assessments. Research assistants and the lead statistician remain blind to trial arm allocation, with the lead statistician not attending the closed part of the Data Safety and Monitoring Board (DSMB) meeting. Any violations of the study protocol are recorded and reported to the Trial Steering Committee and the DSMB.

#### Data collection methods

All data are collected and handled in accordance with PRIMENT Standard Operating Procedures (SOPs). A unique identification number is assigned to each participant and all identifying participant information is stored separately and securely in UCL Data Safe Haven, a secure system for storing sensitive study information. Source data verification checks will be completed on 100% of the primary outcome measure, as well as for 5% of all secondary outcome measures. The delegation log identifies all those personnel with responsibilities for data collection and handling, including those who have access to the trial database.

Long-term experience of studies with people with ID suggests that very few are lost to follow up (e.g. PBS study, TIME-A study). Participants may still wish to meet with the researchers but not take part in interventions. Therefore, although we shall stress that participants can withdraw at any time without giving a reason, we shall retain any assessment records that have been carried out to that point and we shall maintain contact unless told otherwise.

#### Data management

Audio and video recordings are stored on Data Safe Haven and are deleted from the digital machines from which they were originally recorded. The CRFs are entered into a web-based clinical data management system, Red Pill, provided by Sealed Envelope through PRIMENT. Original copies of outcome measures are stored in locked cabinets in a locked office. At the end of the trial, prior to analysis, PRIMENT SOP Database Lock, Unlock and Closure will be followed. All aspects of data management of the study comply with the UK Data Protection Act 1998, PRIMENT SOPs, GDPR and Good Clinical Practice.

#### Patient and public involvement

Parents of children with ID and challenging behaviour from the Camden Special Needs Forum assisted in the development of the study proposal. Four parent members of the national charity CONTACT were also recruited to form the Parent Advisory Group (PAG), meeting four times annually to assist in overseeing the trial, discussing study progress and helping with materials. The PAG will be involved with reviewing the full study report and dissemination plan.

#### Process evaluation

To understand how psychosocial interventions work in practice, particularly due to the paucity of SSTP delivery within the UK NHS, a process evaluation utilising a mixed methods approach has been included within the trial. This includes assessment of what is delivered (fidelity, dose, adaptations, reach), collection of the opinions of a stratified purposive stakeholder sample, i.e. participants (those in the intervention/TAU groups, as well as those who have declined, approximately 10–12 from each); 6–8 service managers; and all therapists. Parents participating in these qualitative interviews receive an additional £15 voucher. Therapists also ask parents in the intervention arm to complete a brief satisfaction questionnaire to assess satisfaction with the intervention at the end of the final group session.

### Statistical methods

#### Analysis of primary outcome

A consort flow diagram [40] is used to describe the progress of participants through the study and the follow-up at different time points. Descriptive analyses (means, standard deviations, relevant quantiles and proportions) will be used to summarise the characteristics of the children in each study arm. A comparison of baseline characteristics will be performed to assess whether balance has been achieved; any notable imbalances may lead to additional adjusted analyses for continuous outcomes.

The primary analysis of the CBCL score at 12 months will use mixed models to perform an individual level analysis and will follow Roberts and Roberts (2005) [41] in adjusting for therapist clustering in the intervention arm only (random coefficient model). The final model will also adjust for baseline CBCL score and randomization stratification factors (centre, level of ID) using fixed effects. All modelling assumptions will be checked and a sensitivity analysis will be performed relaxing the heteroscedasticity assumption. Significance will be considered at the 5% level and confidence intervals with be at the 95% level.

Additional analyses will be performed for the secondary outcomes. Continuous outcomes will be analysed using a similar modelling approach to that described for the primary outcome, but for binary outcomes we shall use logistic mixed models [42]. The amount of missing data in each trial arm will be reported and we will investigate its impact on the balance achieved by randomisation. We will also explore whether missingness is associated with any participant characteristics, using descriptive comparisons and tests as appropriate. This may lead to further adjusted analyses. Stata 15 and R 3.6.0 or above will be used to perform the analyses.

#### Economic evaluation

The economic evaluation will be conducted from a health and social care perspective in the primary analysis, and from a societal perspective in a secondary analysis, which includes the impact on quality of life of parents and other caregivers contributing to the child’s care. The Child and Adolescent Service Use Schedule (CA-SUS) [43] tracks the personal, societal and health service resource usage in the past 6 months at baseline and 12-month follow-up and in the past 4 months at 4-month follow-up. The primary analysis will include only health and social care data collected as part of the trial, meaning this will only cover 10 months of the trial (missing months 4 to 6). Sensitivity analyses will be used to project costs from the follow-ups to estimate the 12-month health and social care resource use. UK unit costs obtained from publicly available sources will be applied to each resource item in both arms of the trial [44, 45]. Benefits payments will be costed from government statistics. Data on delivery of the intervention will be collected to calculate the cost of the intervention using micro-costing methods [46].

The overall economic evaluation will comprise: 1) Cost-effectiveness analysis estimating the mean incremental cost per change in CBCL; 2) Exploratory analysis of quality of life using the PedsQL to predict utility scores. There is no single, valid, preference-based measure for health state valuation in children under the age of 5 or children with ID and therefore it is not currently possible to calculate Quality-Adjusted Life Years (QALYs) for use in cost-utility analysis [47]. Therefore, the PedsOL and the mapped EQ-5D-Y utility scores algorithm [48, 49] will be utilised to calculate QALYs; 3). Cost-benefit analysis of the impact on the parents/caregivers.

Cost and effect data will be combined to calculate incremental cost-effectiveness ratios for each analysis. We shall use non-parametric bootstrap estimation to derive 95% confidence intervals for mean cost and effect differences between the trial groups and to calculate 95% confidence intervals around the incremental cost-effectiveness ratios. We will include adjustments for baseline values (costs, CBCL and effects) in the three analyses. Cost-effectiveness acceptability curves, showing the percentage of cases for which, the intervention is cost-effective will be constructed using the bootstrap data. A series of sensitivity analyses will be undertaken to explore the implications of uncertainty on the incremental cost-effectiveness ratios.

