### Sample size

A sample of 258 children (SSTP: 155 children, TAU: 103 children) will allow us to detect a low to moderate (standardised) effect size of 0.40 for the primary outcome at the 5% significance level, with 90% power. This is equivalent to detecting a clinically meaningful difference between the two treatment groups of 8 points, assuming a standard deviation of 20. This calculation is based on baseline-adjusted (ANCOVA) analysis assuming a correlation of 0.5 between baseline and follow-up measurements. In addition, the calculation has been adjusted for therapist clustering, assuming an intra-class correlation of 0.05, average group size of 7, and an anticipated drop-out of 10%.

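### Bootstrap intervals around the ICER are planned without condition, and the economic section does not carry over the SSTP-arm clustering that the clinical analysis allows for

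*Protocol article*

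**What the plan says.** The Economic evaluation section states: "We shall use non-parametric bootstrap estimation to derive 95% confidence intervals for mean cost and effect differences between the trial groups". The same bootstrap is then used "to calculate 95% confidence intervals around the incremental cost-effectiveness ratios". An ICER is to be produced in each of the planned analyses, and no condition is attached to its interval. The listed adjustments are baseline costs, CBCL and effects. Acceptability curves will be drawn from the same replicates, and sensitivity analyses on the ICERs are promised. The section mentions neither a resampling unit nor therapist or group clustering.

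Elsewhere the article treats clustering as material. The Sample size section says the calculation was "adjusted for therapist clustering, assuming an intra-class correlation of 0.05, average group size of 7". The analysis of the primary outcome fits a random coefficient for therapist in the SSTP arm only. The effect measure in the cost-effectiveness analysis is the CBCL, the same outcome as in that model.

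**The concern.** There are two issues, the first the more important.

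**Interval for a ratio.** An ICER is ΔC/ΔE. A negative value can mean that SSTP is cheaper and better or that it is dearer and worse, and the ratio diverges as ΔE approaches zero. Once replicates lie on both sides of ΔE = 0, sorting them by ratio mixes opposite conclusions. Any bounded interval is then misleading, because when the 95% interval for ΔE includes zero, the Fieller confidence set for the ratio is not a bounded interval. The article itself allows for a null result: the Dissemination policy section discusses a negative trial in which usual care may do as well, and the Treatment as usual section lists evidence-based parenting programmes in the comparator.

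**Clustering.** As written, the trial could publish two different 95% intervals for one CBCL contrast, one allowing for SSTP-arm clustering and one not. Sessions are delivered in groups, so intervention cost is plausibly shared within a group as well. The economic results are meant to inform recommendations to providers, so the uncertainty around them should be on the same footing as in the clinical analysis.

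**Working it through.** **Inputs (Sample size section).** "effect size of 0.40 for the primary outcome at the 5% significance level, with 90% power"; "difference between the two treatment groups of 8 points, assuming a standard deviation of 20"; "baseline-adjusted (ANCOVA) analysis assuming a correlation of 0.5 between baseline and follow-up measurements"; ICC 0.05, group size 7, drop-out 10%; 155 SSTP and 103 TAU. A two-sided test is assumed, as sidedness is not stated.

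**Step 1: reproduce the sample size.**
- Adjusted SD = 20 × √(1 − 0.5²) = 17.32.
- Design effect = 1 + (7 − 1) × 0.05 = 1.30, in the SSTP arm only.
- TAU n = (17.32/8)² × (1.96 + 1.2816)² × (1.30/1.5 + 1) = 91.9, rounded up to 92.
- 92/0.9 gives 103; 1.5 × 103 gives 155; the total is 258, as stated.
- A design effect in both arms would give about 296. The stated figure therefore rests on SSTP-arm clustering.

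**Step 2: SE of the CBCL difference after drop-out** (155 × 0.9 = 139.5; 103 × 0.9 = 92.7).
- With SSTP-arm clustering: 17.32 × √(1.30/139.5 + 1/92.7) = 2.456.
- Without: 17.32 × √(1/139.5 + 1/92.7) = 2.321.

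**Step 3: behaviour of the ratio.** The share of replicates with the opposite effect sign is Φ(−d/2.456), where d is the observed difference. The chance that the 95% interval for the effect includes zero is Φ(1.96 − δ/2.456) − Φ(−1.96 − δ/2.456), where δ is the true difference.

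| CBCL difference | Replicates with reversed sign (if observed) | Effect interval includes zero (if true) |
|---|---|---|
| 8 | 0.06% | 10% |
| 4 | 5% | 63% |
| 2 | 21% | 87% |
| 0 | 50% | 95% |

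**Step 4: if individual children were resampled.**
- SE ratio = 2.456/2.321 = 1.058.
- The interval is 1 − 1/1.058 = 5.5% too narrow.
- Coverage = 2Φ(1.96/1.058) − 1 = 93.6%.

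**Step 5: range under assumptions.** No ICC for costs is given. The larger cluster size below assumes the analysed SSTP children are spread evenly over the eight therapists (139.5/8 ≈ 17.4).

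| ICC | Size 7: too narrow by (coverage) | Size 17.4: too narrow by (coverage) |
|---|---|---|
| 0 | 0% (95%) | 0% (95%) |
| 0.01 | 1.2% (94.7%) | 3.1% (94.2%) |
| 0.05 | 5.5% (93.6%) | 13.2% (91.1%) |
| 0.10 | 10.2% (92.2%) | 22.3% (87.2%) |

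**Step 6: simulation check at ICC 0.05** (1,500 trials, 400 bootstrap replicates each).
- 20 groups of 7: mean interval width was 0.514 SD with individual resampling and 0.540 SD with group resampling.
- 8 therapists with 17 children each: coverage was 90.6% with individual resampling and 93.0% with therapist resampling. Resampling only eight clusters therefore still under-covers.

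**The case against.** **The resampling unit is unstated, not wrong.** A reader might infer that the plan uses a plain bootstrap of individual children and that its intervals are therefore too narrow. The article does not say so. A non-parametric bootstrap can resample groups or refit a clustered model, and a condensed article may leave that detail to a fuller document. This stands. What remains is that the section lists its adjustments and omits the one that the clinical analysis applies to the same contrast.

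**The clustering effect is modest.** This also stands. The 13% figure might be read as the plan's own, but it rests on an assumed therapist cluster of about 17, whereas the article pairs ICC 0.05 with a group size of 7. The Trial status section reports 190 randomised and 19 completed groups. At 3:2 that is about 114 SSTP children, so at most about 6 per completed group on average. The design effect is then 1.25, the SE ratio √((1.25/1.5 + 1)/(1/1.5 + 1)) = 1.049, and coverage about 93.8%.

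**The plan already limits the ratio problem.** Separate intervals for cost and effect would show whether the effect interval includes zero, and acceptability curves need no ordering of ratios. At the design effect of 8 points (8/2.456 ≈ 3.3 SE) sign reversal is negligible. Nor does the article name the percentile method. All of this is correct but only a partial answer: the ICER interval is still promised in every analysis, and no way of constructing a bounded interval makes it meaningful when the effect may be zero.

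**Conclusion.** The point holds in a conditional form. The unconditional ICER interval is a stated choice that works if the effect is near 8 points and fails if it is small: about one replicate in five changes sign at an observed 2 points, and half do at 0. These figures rest on the plan's SD, correlation, ICC, group size and drop-out, and on a normal approximation. They concern the CBCL analysis. The article gives nothing from which to size the same problem for QALYs, so a claim that their effect is likely to be small has no support in it.

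The clustering part is smaller. If children were resampled individually, the effect interval would be about 5.5% too narrow under the plan's own inputs. It would be worse only with larger clusters or a higher ICC for costs, neither of which the article gives. That the economic intervals are in fact too narrow is not established. No stated figure is wrong, and the sample size reproduces.

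**What to change.** 1. Replace the ICER interval with incremental net benefit, λΔE − ΔC, and its 95% interval over a pre-stated range of threshold values λ. Net benefit is linear in both differences, so it has no quadrant problem, and it comes from the same replicates. Show it with the cost-effectiveness plane and the acceptability curves already planned, and report the ICER as a point estimate. Doing this in all cases avoids a reporting rule that depends on the result.
2. State how the SSTP-arm clustering enters the economic analysis. One option is to resample whole SSTP groups and individual TAU children. Because there are only eight therapists, and a therapist-level bootstrap under-covers, a cluster-adjusted regression of costs and effects, or of net benefit, is an alternative.

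The cost is a few sentences in the economic plan, a little more analysis code and slightly wider intervals. No new data are needed.

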#### Data monitoring

The study is overseen by a Data Safety and Monitoring Board (DSMB) which has six monthly meetings to manage trial procedures. Members have no competing interests and are independent from the study sponsor and organisers. Interim analyses are supplied to the DSMB which advise the Trial Steering Committee (TSC) on whether the active intervention is successful and whether the economic outcomes evidence is sufficient to guide recommendations for SSTP to health care providers. No interim analyses are planned.

#### Harms

Serious Adverse Events (SAE; untoward occurrences that result in harm) are reported via the eCRF by the trial manager within 24 h of becoming aware of the event. All reports are reviewed by the CI or PIs within 2 days of receiving the report and the outcome is recorded in the eCRF. SAEs that are determined to be related and unexpected are reported to the ethics committee and to PRIMENT, in accordance with the PRIMENT non-clinical trial of an investigational medicinal product (Non-CTIMP) safety management SOP.

#### Auditing

Site visits are conducted at all sites annually. The site file, consent forms, enrolment and screening logs are checked and source data verification checks are conducted. A monitoring report is usually compiled and reviewed by PRIMENT.

#### Confidentiality

All study-related information is stored securely at the study site. All participant information is stored in locked file cabinets in locked rooms with limited access and data is also stored through the secure online system, Data Safe Haven. Data is identified by identification numbers to maintain participant confidentiality. Personal information is stored separately from the study records.

#### Dissemination policy

The study papers will be published in high impact journals and targeted communications for parents will be published through the charity Contact. Contact will also advise on other media and policy opportunities that allow for dissemination. Findings will be communicated at local, national and international conferences including for lay and parent groups. A study report for the funders will be posted on the HTA website. Parents will be involved at all stages and take part in commenting on reports and papers prior to publication as well as leading on presentations. In the event of a negative trial, it is important to know whether treatment as usual as currently provided in the services in England may be as effective as a manualised intervention. Therefore, the study, regardless of outcome, will be published and disseminated. All co-applicants will be listed as authors. The protocol will be published in an open access journal; the dataset and statistical codes will be available by sharing agreements upon request.

#### Trial status

Participant recruitment in this study commenced in September 2017. A 10-month internal pilot tested feasibility, acceptability and recruitment at all sites, using the full baseline and eligibility and follow-up assessment battery for all cases and the start-up of SSTP delivery to some of the participants. The progression criterion was that the rate of recruitment between months 5–14 should be at least 70% of the rate expected (no fewer than 8 children per month). This was achieved and the Trial Steering Committee advised NIHR to proceed to the full trial. The study is actively recruiting. To date, 190 participants have been randomised into the study and 19 groups have been completed.

## Discussion

This paper describes the study protocol for a multicentre trial designed to investigate the clinical and cost-effectiveness of a parent mediated intervention (SSTP) to reduce challenging behaviour in pre-schoolers with moderate to severe ID. Challenging behaviour is prevalent and persistent in children with moderate to severe ID and is associated with many negative outcomes, including later psychiatric morbidity [4, 50–52], poorer quality of life, parental stress and high service costs [53–56].

SSTP is a parenting programme that has demonstrated efficacy in non-UK randomised controlled trials to reduce challenging behaviour in children and improve parent outcomes [19, 57, 58]. A recent meta-analysis of 16 studies has highlighted the large evidence base for Level 4 SSTP, which had the strongest treatment effects compared to other SSTP levels for improving behaviour in children with ID [20]. However, the majority of studies included small sample sizes (mean = 60.2, SD = 43.8) and randomised control trials of SSTP have not been conducted in the UK to compare this intervention to other readily available therapies.

To our knowledge, this is the first UK trial to evaluate the effectiveness of SSTP as a parent mediated intervention for challenging behaviour in very young children. The findings will inform real-world practice and NICE clinical recommendations about the provision of group interventions for children with moderate to severe ID [51]. We have already identified significant variability in available services for this population across the 4 sites in the UK and therefore, rolling out the intervention should be underpinned by appropriate evidence.

The study has several strengths, it is multicentre and is powered to detect a significant difference between intervention and TAU arms. The primary study outcome measure (CBCL) is a robust and widely validated measure of behaviour, which will be further validated through the use of behavioural observations of challenging behaviour at each time point. Additionally, data from multiple respondents is being collected on the CBCL (e.g. parents and another caregiver such as a teacher) to examine accuracy and enable the potential measurement and comparison of behaviours across different contexts and with different caregivers. The secondary outcome measures will also provide critical information on variables that are known to impact child behaviour [59, 60]. Moreover, conducting a process evaluation and fidelity testing ensures the external validity of the study and will examine gaps in the implementation that are likely to hinder uptake [61].

Limitations include the lack of blinding of participants, potential attrition of participants and deviations in the delivery of the intervention. Further, only parents with sufficient English to respond to the questionnaires and follow the intervention guidance can be recruited into the study.

In conclusion, the results of the trial described in this protocol will provide a vital contribution to intervention research for reducing challenging behaviour in children with ID. This population is said to be underserved, with almost no access to evidence based interventions for challenging behaviour early in life [62]. The trial will inform policy on the clinical and cost-effectiveness of SSTP, with the aim of improving behaviour and outcomes for children with moderate to severe ID and their families.

